#### Design and Content of Treatment

The 4 distinct ICBT programs used in this study are targeted children (8-12 years), adolescents (13-17 years), and the parents of each group, respectively. The treatment lasts for 10 weeks and consists of 10 modules for children, adolescents, and parents of children (with a new module every week) and 5 modules for parents of adolescents (with a new module every other week). An overview of treatment content can be seen in Table 1. The programs include sections with videos, exercises, and quizzes designed to actively engage the child or adolescent in the treatment. Psychoeducation regarding FAPDs, detection of avoidance behavior, a brief mindfulness exercise called “SOL (Stop, observe, let go)” and graded repeated exposure exercises comprise some of the central components covered in the programs for both children and adolescents. The first modules of treatment introduce the above-mentioned concepts whereas later modules focus on repeated exposures. The purpose of “SOL” is Stopping, Observing how the stomach feels, and Letting go of the focus on the stomach and continuing with the activity. The parental programs emphasize supporting their child or adolescent’s exposure, decreasing attention to their child or adolescent’s abdominal symptoms, and prioritizing shared positive activities. Each module ends with planning of the homework assignments which are evaluated first thing in the next module.

**Table 1 table1:** Overview of the content of treatment for each module.

Module	Children (8-12 years)	Parents	Adolescents (13-17 years)	Parents
1	Introduction to the treatment format Psychoeducation on FAPDs^a^ (video) Mapping “stomach behaviors” (control, avoidance, safety) Setting treatment goals Homework: Self-monitoring	Introduction to the treatment format Positive attention Focus shift Mapping common parental behaviors Handling personal frustrations Homework: Focus shift, breaks, involving peers	Introduction to the treatment format Psychoeducation on FAPDs (video) Setting treatment goals Homework: self-monitoring	Introduction to the treatment format Focus on positive attention and shared moments Mapping common parental behaviors Homework: Shared positive moments

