2	Psychoeducation on impact of thoughts and “SOL”^b^ (video) Constructing an exposure hierarchy. Homework: Utilize “SOL” in everyday situations.	Golden moments Board game with rewards for exposure exercises. Homework: Golden moments, focus shift, planning rewards”	Mapping “stomach behaviors” (control, avoidance, safety) Behavior analysis Homework: Behavioral experiment (avoiding “stomach behaviors”)	
3	Behavior analysis Psychoeducation on exposure exercises (video) Homework: Exposure exercises.	Supporting child’s exposure exercises Managing school absences Homework: board game rewards, golden moments, focus shift	Psychoeducation on impact of thoughts and “SOL” (video) Toilet habits (frequent visits, urgency) Homework: “SOL” and new toilet habits	Psychoeducation on FAPDs (video) Acknowledging and shifting focus to reduce symptom focus Homework: Shared positive moments, letting go of parental behaviors, focusing on alternative adolescent behaviors
4	Toilet Habits (frequent visits, urgency) Behavior analysis Homework: Exposure exercises, new toilet habits, “SOL”	Parental stress and recreational activities Homework: recreation, golden moments, board game rewards, focus shift	Psychoeducation on exposure exercises (video) Behavior analyses Construct exposure hierarchy Homework: “SOL,” toilet habits, finish exposure hierarchy	
5	Repetition Behavior Analysis Homework: Exposure exercises, toilet habits, eliminating safety behaviors, “SOL”	Repetition Mapping challenges Homework: recreation, golden moments, board game rewards, focus shift	Exposure exercises Anticipatory anxiety Emotional versus behavioral goals Homework: Exposure exercises, “SOL,” toilet habits.	Encourage and support the adolescent’s exposure Psychoeducation on exposure exercises (video) Homework: Shared positive moments, support and encouragement, support adolescent’s exposure
6	Positive analysis of new behaviors Advancing exposure difficulty Homework: Advancing exposure exercises, toilet habits, “SOL”	Problem-solving with child Homework: recreation, golden moments, board game rewards, focus shift, problem-solving	Further details on exposure and rewards Homework: Exposure exercises, “SOL,” and toilet habits	

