### Measures

#### Measures in the Single Case Design Study (Substudy 1)

Children and adolescents will answer a daily short questionnaire (DSQ) throughout a pretreatment baseline period, randomized to last between 5 and 15 days, throughout the 10 weeks of treatment, and for a final 7-day follow-up period 3 months after treatment. The DSQ is an 8-item questionnaire, designed in line with the SCRIBE (Single-Case Reporting guideline In BEhavioural interventions) guidelines [32], addressing specific targets of the intervention, with items from different validated questionnaires for children and adolescents [32,33]. The full DSQ questionnaire is shown in Textbox 1. The primary outcome in the SCED study is the level of gastrointestinal symptoms assessed using 2 items from the Pediatric Quality of Life Inventory (PedsQL) Gastrointestinal Symptoms Questionnaire [34]. Secondary outcomes include illness worries, avoidance behavior, and level of pain acceptance as measured by the Visceral Sensitivity Index (VSI), irritable bowel syndrome behavioral response questionnaire (IBS-BRQ), and the Chronic Pain Acceptance Questionnaire – Adolescent Short Form (CPAQ-A8), respectively [35-37]. The items have been modified into questions concerning the last 24 hours and are rated on a 0-10 scale (“not at all” 0, “all the time” 10).

Daily short questionnaire (DSQ).During the last 24 hours, on a scale from 0 (not at all) to 10 (all the time)1) Did your stomach hurt?2) Did you feel discomfort in your stomach?3) Did you worry about the problems in your belly?4) Were you frightened when you felt discomfort in your belly?5) Did you avoid going out in case you had belly problems?6) Did you spent more time on the toilet than you ideally would like?7) Did you do things that are important and things that are fun even though you have problems in your belly?8) Has the most important thing been to keep your symptoms under control whenever you did something?

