### Sample Sizes

According to research design standards [65], a minimum of 3 replications are recommended in a SCED study (substudy 1). However, to achieve sufficient power for randomization tests, a higher number of potential randomizations is recommended [66]. The number of randomizations is influenced by both the number of participants and the number of possible starting points; hence, guided by Levin et al [67], we chose 6 participants in each group.

For substudy 2, we based our power analysis on potential differences in cognitive bias and interoception between cases and healthy controls on a previous similar study on cognitive bias in children and adolescents [40] and studies on interoceptive accuracy in adults with functional disorders [68-69]. Based on these study findings, calculations show that in order to detect a minimum effect size of 0.5 (Cohen *d*), 60 patients and 100 healthy controls are required for the cognitive bias outcome, and a minimum of 51 patients and 51 healthy controls for the interoception outcome to achieve 80% power at an α level of .05. The subsequent analysis of the possible impact of treatment on these 2 factors is more explorative and therefore no a priori power calculation is provided. The same concerns the last study on parental factors (substudy 3) as possible effect moderators. However, here the sample size is the largest possible, comprised of parents from substudies 1 and 2.

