### Data Analyses

In substudy 1, visual inspection analyses will be applied to demonstrate the effect of the intervention on all outcomes [71]. In addition, within-case effect size measurements will be calculated using Tau-U [72] and between-case effect sizes will be determined using hierarchical linear regression models to account for the serial dependency of data [73]. A randomization test will be applied to test differences in means for the baseline versus treatment, and baseline versus follow-up periods, respectively [74].

In substudy 2, participants’ descriptions reported in the recall phase of the BY-GIS task will be coded to their corresponding word or picture and category presented in the encoding phase (eg, picture-description “children and cake” coded as the birthday picture within the fun category). Coding for the first 20% of participants will be conducted by 2 independent raters ([name] and [name]). If the consensus rating exceeds 90%, 1 rater will code the remaining cases independently. A third and experienced rater ([name]) may be consulted to resolve potential disagreements. Baseline data will be analyzed descriptively and compared with (1) data from a healthy control group who performed the same experimental test [38], and (2) end-of-treatment data, exploring potential differences in the outcomes from the encoding, recall, and recognition phases using *t* tests or nonparametric tests, depending on data variability in the samples.

Baseline measures of interoceptive performance and metacognitive measures will be analyzed descriptively and compared with (1) measures from a healthy control group and (2) end-of-treatment measures, using *t* tests or nonparametric tests, depending on data variability in the samples.

In substudy 3, the potential moderation of parental factors on treatment adherence (number of completed modules) and main measure (gastrointestinal symptoms) for children or adolescents will be investigated using negative binomial regression and linear mixed models, respectively, adjusting for baseline parental distress, illness worries, and illness behavior, respectively.

In addition, the potential effect of treatment on these parental factors and all other child or adolescent measures will be analyzed using linear mixed regression models.

An experienced statistician will provide statistical support for all analyses.

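### Substudy 1's randomization test on phase means detects only change within a few days of treatment start, although exposure begins in week 3 (children) or week 5 (adolescents)

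*Protocol article*

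**What the plan says.** Under Measures in the Single Case Design Study, the pretreatment baseline is "randomized to last between 5 and 15 days", and daily ratings continue "throughout the 10 weeks of treatment, and for a final 7-day follow-up period 3 months after treatment". Under Data Analyses, a randomization test is planned "to test differences in means for the baseline versus treatment", and likewise for baseline against the follow-up period. No lag and no late-treatment window is mentioned.

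Sample Sizes justifies six participants per age group by the number of possible randomizations: "to achieve sufficient power for randomization tests, a higher number of potential randomizations is recommended". It gives no power figure, effect size or assumed time of onset for substudy 1.

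Design and Content of Treatment sets one module per week for children and adolescents and adds: "The first modules of treatment introduce the above-mentioned concepts whereas later modules focus on repeated exposures". In Table 1 the first exposure homework for children is in module 3 ("Psychoeducation on exposure exercises (video) Homework: Exposure exercises"). For adolescents it is in module 5 ("Emotional versus behavioral goals Homework: Exposure exercises"); their module 4 only prepares the exposure hierarchy. The Introduction describes symptom relief as following gradually from exposure.

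**The concern.** A start-point randomization test draws its evidence from one comparison: is the statistic larger at the real start day than at the other days that could have been drawn? With a phase-mean statistic, this works if symptoms shift at the start. If the shift comes a week or more later, nearly all candidate start days lie before it, and the ranking of the real day among them says almost nothing about treatment.

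The protocol's own timetable points to delay for the exposure component. At stake are the sample-size rationale, which rests on this test, and the reading of a null p-value, which could be taken as evidence against an effect that the test could not have seen.

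**Working it through.** **Inputs from the protocol.** Start days 5 to 15, so 11 per participant if every day is allowed. Treatment of 10 × 7 = 70 days. Six participants per group. Exposure from module 3 (treatment day 2 × 7 + 1 = 15, a lag of 14 days) or module 5 (day 4 × 7 + 1 = 29, a lag of 28 days).

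**Assumed, because not stated for substudy 1.** Alpha .05; one- and two-sided versions; step effects of 1, 2 or 3 within-person SD; first-order autocorrelation of 0 or 0.3. The protocol gives no power figure for this substudy, so there is none to reproduce.

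**Mechanism, without noise.** Take a true start after day 10, a series of 10 + 70 = 80 days and a drop of size d. For a candidate cut k at or before the change, the difference (baseline mean minus treatment mean) is d × (days after the change) / (80 − k).

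- Immediate drop (70 changed days): k = 5 gives 70/75 = 0.93d; k = 10 gives 70/70 = 1.00d. At k = 15, five changed days fall into the baseline, which gives d − (5/15)d = 0.67d. The peak is at the true start.
- Drop 14 days after start (56 changed days): k = 5 gives 56/75 = 0.75d; k = 10 gives 56/70 = 0.80d; k = 15 gives 56/65 = 0.86d. The statistic simply rises with k, and the true start has no special place. A larger d scales all three values alike.

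In the follow-up comparison the follow-up mean is the same for every candidate. Only the baseline mean moves with k, so a change after day 15 leaves no trace of the true start.

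**Simulation.** 800 data sets per cell (simulation error about 0.8 points near 5%). The statistic is averaged over participants, and start days are redrawn within days 5 to 15. Two schemes were used: independent starts (11^6 = 1,771,561 assignments, 999 redraws) and six staggered starts permuted (720, exact). With no effect, rejection was 5.1%.

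| Onset after start (step of 1-3 SD, autocorrelation 0-0.3, one-sided, six participants) | Power |
|---|---|
| 0 days | 57-100% |
| 2 days | 17-76% |
| 4 days | 9-19% |
| 7 days | 4.0-6.8% |
| 14 days (children's exposure) | 3.1-6.2% |
| 28 days (adolescents' exposure) | 2.6-5.9% |

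**Variations.**
- Two-sided (autocorrelation 0.3, 1-2 SD): 45-83% for immediate onset, 4.1-6.4% at lags of 7 to 28 days.
- All 12 participants pooled: 4.0-5.2% at lags of 7 to 28 days.
- Fixed 85-day series: 3.2-6.2% at lags of 7 to 28 days.
- Linear improvement from day 1 (autocorrelation 0.3): 10-29% if complete after 14 days, 7-13% after 28 days, 5-9% after 70 days.
- Baseline versus follow-up: 5.9-6.5% at a lag of 7 days, 5.0-5.8% at 14 days.

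**The case against.** **Active content starts before exposure.** Both age groups get psychoeducation and self-monitoring in module 1. Children get the mindfulness exercise and adolescents a behavioral experiment in module 2, and parents change their responses from the outset. The daily questionnaire also covers worry, fear and avoidance, which may move early. This stands: no data in the article fix the onset, and with an immediate shift the planned test is useful. The point is conditional on onset.

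**The test is one of four analyses.** A reader might infer that a large true effect would be reported as unsupported. The protocol does not support that. Visual inspection is listed first as the means of demonstrating effect; Tau-U and hierarchical regression follow; none of these depends on ranking the start day. Nor does the article say that the conclusion rests on the randomization test.

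**The detail may sit elsewhere.** The article is condensed, and an analysis plan not shown could define a lag. However, the article itself states both the 5-15 day window and a difference in phase means, and it states the power rationale without any condition on onset.

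**Substudy 1 is finalized.** The Results section says so. This stands: a new statistic would now be chosen after data collection and cannot replace the planned test.

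**Conclusion.** The point holds, confined to the two randomization tests. They are sensitive to change within the first few days of treatment and close to uninformative (about 3-7% power at a nominal 5%) if onset is 7 or more days after start. Larger effects or pooling the age groups do not restore power. The claim of sufficient power under Sample Sizes therefore holds only for near-immediate onset; the number of possible randomizations is ample but does not help here.

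The figures rest on assumed effect sizes, autocorrelation, alpha and sidedness. The collapse at lags of a week or more appeared under every variant tried and follows from the mechanism above. It does not follow that substudy 1 cannot show an effect, or that its other analyses are weakened.

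**What to change.** 1. Keep the planned test, but call it a test of immediate effect. Restate the Sample Sizes rationale to match, and say that a null in either comparison is not evidence against a delayed or gradual effect.

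2. Add a supplementary analysis, labelled as specified after data collection, with lags chosen without looking at outcomes:
   - *Abrupt change.* For each candidate set of start days, compare short windows (for example 7 days) before and after start + lag, using one common lag for all participants. Take the maximum over every daily lag, for example 0 to 35 days.
   - *Gradual change.* Use a ramp statistic beginning at start + lag, with lags from Table 1 (14 days for children, 28 for adolescents).
   - Recompute the whole statistic, including any maximum, within every re-randomization so that the test stays exact.

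For six participants, autocorrelation 0.3 and an abrupt 2 SD drop, the daily-lag maximum gives 94-96% power at the onsets tested. A few fixed lags (0, 7, 14, 21, 28) should not be used instead: power falls to about 6% for a drop at day 17, to 18% if onset varies over days 14 to 20, and is 5-9% for a 28-day ramp. The ramp statistic at the correct lag gives about 70% for a 28-day ramp of 3 SD.

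**Cost.** Extra analysis work and a multiplicity caveat for the added tests; data collection is unchanged. Power stays well below these figures when onset differs between participants (about 44% for the daily-lag maximum with onset spread over a week), or when change is slow and the lag is wrong. The supplementary tests reduce the problem but do not remove it.

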For both studies in substudy 2, we will perform parallel studies on healthy controls. The BY-GIS task was already tested in 96 healthy controls [38], and the interoception test setup will be performed in 60 healthy controls (all aged 8-17 years).

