## Results

Recruitment of participants began in June 2022. Substudy 1 is finalized and expected to be published in 2025. Recruitment for substudies 2 and 3 is ongoing. By November 2024, 45 children and 24 adolescents have been included. Due to a skewed distribution in referrals, with a predominance of referrals on children, we continue to include children and adolescents until we have reached 30 adolescents. Inclusion is expected to be completed by January 2025 and data collection in March 2025.

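### Coder agreement for BY-GIS free recall is checked only on the first 20% of participants, so drift in the later single-rater coding would go unseen

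*Protocol article*

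**What the plan says.** In the protocol article, Data Analyses (substudy 2), free-recall "descriptions reported in the recall phase of the BY-GIS task will be coded to their corresponding word or picture and category" shown at encoding. The reliability rule is explicit: "Coding for the first 20% of participants will be conducted by 2 independent raters", and then "If the consensus rating exceeds 90%, 1 rater will code the remaining cases independently". A third, experienced rater "may be consulted to resolve potential disagreements".

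The coded baseline data are to be "compared with (1) data from a healthy control group who performed the same experimental test", and also with "end-of-treatment data, exploring potential differences in the outcomes from the encoding, recall, and recognition phases". Measures on Cognitive Bias and Interoception (Substudy 2) reports that 96 healthy controls had already done the task in a separate cited study. The same section describes encoding as participants' own ratings and recognition as participants' own marks, so free recall is the only phase of the three that a rater codes.

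Sample Sizes asks for 60 patients and 100 controls for the cognitive bias outcome, to detect a standardised difference of 0.5. It calls the analysis of treatment impact on this outcome more explorative.

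**The concern.** The article fixes the share, how it is chosen, the threshold and what follows from passing it. Agreement is established once, on the earliest block, and is then taken to hold for the remaining four fifths. Coding habits can change as a rater meets more descriptions. A block drawn from the start cannot show such a change, whether *first* means order of enrolment or order of coding.

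In many studies drift would only add noise. Here it could line up with the comparisons of interest. Controls were tested before the patients, and each patient's end-of-treatment record follows the baseline record. If coding follows the calendar, a shift in how ambiguous descriptions are credited becomes a difference between groups or between time points. It could create an apparent recall bias, or an apparent change in one, and it could equally hide a real one.

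**Working it through.** The plan gives no figure for coding reliability beyond the 90% threshold, so there is none of its own to reproduce. The check has three parts.

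**1. How much rests on one rater.** Planned patients in substudy 2: 60.
- Double-coded: 0.20 × 60 = 12.
- Single-coded: 60 − 12 = 48, or 80%.

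The Results section says "By November 2024, 45 children and 24 adolescents have been included" and that inclusion of both age groups continues until there are 30 adolescents. The final number may therefore differ from 60 (20% of 69 would be 13.8), but the share stays the same. If *first* means enrolment order and early intake had the same age mix as the November 2024 total, adolescents in the block would number 24/69 × 12 ≈ 4, against 6 under the planned equal split. Both conditions are assumptions.

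**2. What is exposed.** Encoding: rated by participants, not exposed. Recognition: marked by participants, not exposed. Free recall: coded by a rater, exposed in both the patient-control and the before-after comparison.

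**3. Sensitivity to a coding shift.** Assumption, not from the documents: coding practice alone moves the recall score of one group or time point by b SD, and the true difference is zero. Two-sided test at .05.
- Between groups, 60 versus 96: noncentrality = b × √(60 × 96 / 156) = 6.076 × b, with 154 degrees of freedom.
- Before-after, 60 pairs, assuming a correlation of 0.5, so that the SD of differences is √(2 × (1 − 0.5)) = 1 SD: noncentrality = b × √60 = 7.746 × b, with 59 degrees of freedom.

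| Assumed shift b | Between groups: noncentrality | Between groups: significant | Before-after: noncentrality | Before-after: significant |
|---|---|---|---|---|
| 0.05 SD | 0.30 | 6.1% | 0.39 | 6.7% |
| 0.10 SD | 0.61 | 9.3% | 0.77 | 11.9% |
| 0.20 SD | 1.22 | 22.7% | 1.55 | 33.2% |
| 0.30 SD | 1.82 | 44.1% | 2.32 | 62.8% |

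A shift in the opposite direction costs power. If the true difference is 0.5 SD, power at 60 versus 96 is 85.5% with no shift, 67.6% with 0.1 SD against it and 44.1% with 0.2 SD against it.

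For scale, 0.2 SD is 0.2/0.5 = 40% of the difference the substudy is sized to detect. The rates show how sensitive the comparison is. They do not estimate what will happen.

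**The case against.** The strongest reply is that coding is mostly matching against a known stimulus list. Recalled words need little interpretation, two raters must agree above 90% before single coding begins, and a third can settle disputes. A shift of 0.3 SD would be 60% of the design difference, which is hard to credit for such a task. At 0.05 SD the error rate stays close to nominal. The before-after analysis is declared explorative. All of this stands, and it limits the likely size of the problem.

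It does not remove the problem. Picture descriptions leave some room for judgement. In the article's own example, a description mentioning cake is assigned to a birthday picture in the fun category, although the task also contains pictures of food. All the stated safeguards operate at the start or on disagreements between raters, and once only one rater is coding there is nothing to disagree with.

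A reader might also infer that raters know which records come from patients and which are end-of-treatment, that patients are coded as a separate batch, or that all BY-GIS scores are at risk. The documents do not support these readings. The article is silent on masking, on batching, on who coded the controls and on whether the 20% includes end-of-treatment records. A condensed article may leave such detail to the full protocol, and it refers to a separate publication for the task procedure. Silence on masking is therefore not counted here as an error. The last reading is wrong, because only recall is rater-coded.

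**Conclusion.** The point holds as a weakness in a stated rule. Agreement is checked on an early block of about 12 of 60 patients, and about 48 are then coded by one rater with no stated later check. Later drift in the recall scores would go undetected and could align with either planned recall comparison.

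Its size is unknown. The between-group range of about 6% to 44% rests wholly on assumed shifts of 0.05 to 0.3 SD with no true difference. The before-after figures also assume 60 pairs and a correlation of 0.5. Nothing in the documents shows that a shift has occurred or will occur. This is a cheap improvement and does not put the substudy's validity in doubt.

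**What to change.** Keep an initial calibration block if the team finds it useful, but base the agreement check on a 20% double-coded set drawn at random over the whole data set, stratified by age group and by time point (baseline, end of treatment).

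Code from an export with ID, group and date removed and the records in random order. Mix in a sample of existing control records where their recall text is available, and compare the new coding of those records with the earlier one. Each part has its own job. The random double-coded set makes drift visible. Random order keeps drift from lining up with time point. Hiding group and time point guards against a leaning that two raters share, which agreement alone cannot reveal. The recoded controls show whether coding is comparable with the earlier study.

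The task data are already collected in REDCap, so this needs an export script and no further patient contact. The cost is that coding finishes later, because it waits for the end-of-treatment records, plus a few extra hours from the same raters.

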## Methods

### Study Design

The study includes 2 recruitment phases. The first phase concerns a single case experimental design (SCED) study (substudy 1) with a total of 12 patients (6 children and 6 adolescents, respectively). The second phase concerns an open pilot study on cognitive biases and interoceptive accuracy (substudy 2) with a total of 60 patients (30 children and 30 adolescents, respectively).

Consequently, a total of 72 children and adolescents, along with a corresponding number of parents, will undergo ICBT for FAPDs throughout the entire study. Parental distress and illness worries will be assessed before, during, and after the treatment in all included parents (substudy 3; Figure 1).

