The study has some limitations. In substudy 1, the generalizability of SCED study results has traditionally been questioned due to the low number of participants. However, our study adheres to guidelines that include multiple data points across different phases, randomization of the length of the baseline phase, and replication across several participants, thereby optimizing generalizability. Furthermore, participants are expected to answer daily questions for an extended period, which could induce some fatigue in responding and potentially affect reliability. Still, the inclusion of several close data points increases precision in analyses and helps buffer against occasional data loss. In addition, the setup was tested on 4 prestudy patients, who reported that the daily questionnaire was easy and quick to answer.

In substudy 2, we use the BY-GIS task, which is newly developed and has not been previously tested in patients. However, the task is developed based on well-known paradigms and previous tests, and it has already been tested in a sample of 96 healthy age-matched controls with good usability [38]. The interoception HRD measures participants’ ability to sense their pulse, which is not directly related to gut sensations but falls within the broader perspective of interoception. However, studies in adults suggest altered interoceptive accuracy across different diagnoses of functional disorders and chronic pain, which indicates that there may be a general hypersensitivity to inner sensations in this patient group as well [86]. Since this study is one of the first to investigate interoceptive accuracy in children and adolescents with FAPDs, we believe it is still valuable to use this well-known and widely used interoception measure.

Substudy 3 is an open pilot trial without a control group for comparison which means conclusions regarding the clinical effect of the treatment should be interpreted with caution. However, the substudy is explorative and primarily aims to investigate new and additional modifiable treatment targets on a parental level.

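### The patient–control tests in substudy 2 carry no age term, although the patient sample has drifted from a planned 50% to about 65% children and control age mixes are not given

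*Protocol article*

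**What the plan says.** All places are in the protocol article.

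- **Analysis of the HRD task (Data Analyses).** "Baseline measures of interoceptive performance and metacognitive measures will be analyzed descriptively and compared with (1) measures from a healthy control group". The test is t or "nonparametric tests, depending on data variability in the samples". No covariate, stratum or matching is named. The BY-GIS outcomes are compared with healthy controls by the same kind of test.
- **Planned mix (Study Design).** Substudy 2 was to have 60 patients, half of them children and half adolescents.
- **Realized mix (Results).** "By November 2024, 45 children and 24 adolescents have been included". Because referrals are skewed towards children, "we continue to include children and adolescents until we have reached 30 adolescents". No cap on children is stated.
- **Controls.** The section on measures of cognitive bias and interoception gives 60 HRD controls and says of both control groups only that they are aged 8 to 17. On the BY-GIS task, the Discussion (Principal Findings) adds that "it has already been tested in a sample of 96 healthy age-matched controls", without saying how they were matched or to what age mix.
- **Power (Sample Sizes).** Both patient–control comparisons are sized to detect d = 0.5 with 80% power at an α of .05: 60 versus 100 for cognitive bias and at least 51 versus 51 for interoception.

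**The concern.** Free recall, recognition, reaction time and psychometric slope plausibly change between ages 8 and 17. The article does not quantify this. It does say that the HRD task had to be shortened and given with spoken guidance for a younger age group, and it treats 8–12 and 13–17 as separate groups throughout.

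If patients are younger on average than controls, an unadjusted two-sample test adds the age effect to the disease effect. Depending on the direction of scoring, this could create a group difference where none exists or hide a real one. Choosing between t and nonparametric tests by data variability does nothing about it. These two comparisons have an a priori sample size, so readers will give them weight. The pre–post comparison is within patients and is not affected by the mix.

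**Working it through.** **1. The plan's own figure.** The 51 versus 51 at d = 0.5 and 80% power is reproduced with a one-sided α of .05 (50 per group by the normal approximation, 51 by the t distribution). A two-sided α of .05 needs 63–64 per group. Sidedness is not stated; two-sided 5% tests are used below. The target of 0.5 serves as the yardstick for the bias.

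**2. Patient age mix.**
- Planned: 30/60 = 50% children.
- November 2024: 45/(45 + 24) = 45/69 = 65.2%.
- If no further child joins and recruitment stops at 30 adolescents: 45/75 = 60%.
- The text leaves open whether the count includes the 6 + 6 patients of substudy 1. If it does, substudy 2 stood at 39/57 = 68.4%, and would end at 39/69 = 56.5% with no more children and 30 adolescents of its own.

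None of these returns to 50%.

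**3. Assumptions, since the document gives no figures.** Control child share c: 50%, varied over 40–65%. Child–adolescent gap D: 0.3–1.0, in units of the SD within an age group. Patients: 60. Controls: 60 (HRD) or 96 (BY-GIS).

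**4. Formulas.** With patient child share p and no disease effect:
- bias = (p − c) × D
- SE² = [1 + p(1 − p)D²]/n_patients + [1 + c(1 − c)D²]/n_controls
- type I error = P(|Z + bias/SE| > 1.96)

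Example: p = 0.652, c = 0.50, D = 1.0, 60 versus 96. Bias = 0.152. SE = √(1.227/60 + 1.25/96) = 0.183. Shift = 0.832. Type I error = 13.2%.

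**5. Results with controls at 50% children.**

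| D (SD) | Bias at 65.2% | Type I, 60 v 60 | Type I, 60 v 96 | Bias at 60% | Type I, 60 v 60 | Type I, 60 v 96 |
|---|---|---|---|---|---|---|
| 0.3 | 0.046 | 5.7% | 5.9% | 0.03 | 5.3% | 5.4% |
| 0.5 | 0.076 | 6.9% | 7.3% | 0.05 | 5.8% | 6.0% |
| 0.8 | 0.122 | 9.5% | 10.6% | 0.08 | 6.9% | 7.4% |
| 1.0 | 0.152 | 11.6% | 13.2% | 0.10 | 7.8% | 8.5% |

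At the current mix the bias is 0.046/0.5 = 9% to 0.152/0.5 = 30% of the target effect. Using all 75 patients of a 45:30 sample moves the last figure from 8.5% to 9.0%: more patients narrow the SE around the same bias.

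**6. Sensitivity to the control mix, patients at 65.2%.**
- Controls 40% children: bias 0.08–0.25 SD, type I error 6.9–28.2%.
- Controls 60%: bias 0.02–0.05 SD, type I error 5.1–5.9%.
- Controls 65%: bias about zero, type I error 5.0%.

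So the unreported control mix decides whether there is a problem at all.

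**The case against.** The strongest reply is that no confounding has been shown. It needs controls with a different age mix from the patients, and neither control mix is reported. The BY-GIS controls are called age-matched, and having been tested earlier does not prove that they fail to fit the realized mix. Age dependence is also assumed. If BY-GIS bias is scored as a contrast between stimulus categories, general age differences in recall would partly cancel; the article does not define the score. All of this stands. A reader might infer that the group differences *are* confounded with age, and the documents do not support that. They show only that nothing in the stated analysis guards against it.

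A reader might also extend the 45:24 ratio to 30 adolescents and expect 45/24 × 30 ≈ 56 children, or 86 patients. That would need 17 more by January 2025, against 69 since June 2022, and the catchment was widened because adolescent referrals were slow. The projection is not used here.

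Nor are these comparisons the study's only ones with a power argument: Sample Sizes also invokes power for the randomization tests of substudy 1.

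Finally, this is a condensed article on an explorative pilot, and covariates are often left to an analysis plan. That carries less weight here. The article names the test, and for substudy 3 the same section names the variables adjusted for. An unseen plan may still add an age term.

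**Conclusion.** The point holds as a gap in protection and should be closed. As stated, the patient–control comparisons on both tasks are unadjusted while the patient sample has moved from 50% to about 65% children, with at least 56.5–60% likely at the end on the readings above. The gap is clearest for interoception, where no matching of the 60 controls is stated. It is weaker for BY-GIS, where the controls are called age-matched without a method or target mix.

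With controls at 50% children and a gap of 0.3–1.0 SD, both assumed, the spurious difference is about 0.05–0.15 SD and type I error about 6–13% at 45:24, or 0.03–0.10 SD and about 5–9% at 45:30. If the controls have the patients' mix, the effect is near zero. The 65% is an interim share of included patients, not a count of those who complete either task.

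**What to change.** In Data Analyses, make the main patient–control comparison for each BY-GIS and HRD outcome a regression on group adjusted for age, either continuous in years or stratified 8–12 and 13–17. Keep the unadjusted test as descriptive. Report the age mix of patients and of each control group, and for BY-GIS state how the 96 controls were matched. If any HRD controls remain to be recruited (the article does not say), frequency-match them to the realized patient age mix.

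The cost is about one degree of freedom. Age should be at hand for everyone, because it decides eligibility in patients and defines the control range. If age does matter, adjustment also gains precision: at a 1-SD gap and an even split, age group explains 0.25/1.25 = 20% of the variance, so the SE falls by about 10% (1 − √0.8). If the groups prove balanced, almost nothing is lost. Adjusting for sex, robust standard errors or special models for counts may be worth considering, but they do not follow from the age imbalance and are not part of this point.
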